### Feasibility outcomes

The feasibility outcome will include an evaluation of eligibility, recruitment and retention rates (in line with CONSORT recommendations), as well as monitoring of completion of outcome measures and assessments. Refusal, withdrawal and dropout from the study protocol will be recorded. Acceptability of the intervention using the cycle ergometer will be assessed by measuring the time to fully perform the exercise and by structured questionnaires with research participants on completion of the intervention. The feasibility of data collection strategies will be assessed descriptively and through item response rates and physical tests.

### Statistical analysis

To describe the sample profile descriptive statistics of numerical variables (scores of scales) will be made.

To compare numerical variables between the two groups at baseline we will use the Mann-Whitney test, due to lack of normal distribution of variables. To compare longitudinal measures between groups and times we will use analysis of variance (ANOVA) for repeated measures, followed by Tukey’s multiple comparison test to compare the groups at all times, and the profile test contrasts to analyze the evolution between assessments in each group. The variables will be transformed into posts (ranks) in the absence of normal distribution.

To estimate the sample size and the power of the sample we will use the sample size calculation for longitudinal studies with repeated measures to compare variables between the two groups (I and II) over the two collection times (pre and post intervention). The significance level will be defined (alpha or Type I error) at 5%, calculating the effect size or delta, which is the expected difference or difference obtained between the group means divided by the standard deviation, and the coefficient of intraclass correlation between repeated measurements. The values of the effect size delta (delta effect size) will vary generally between 0 and 3. Delta values of 0.25, 0.75 and 1.25 respectively correspond to small, medium or large effects. Subsequently, the power of the sample and the sample size will be obtained by setting the power at 80% or Type II error (1-beta) at 20%. The significance level for statistical tests will be 5% (*P* < 0.05).

Statistical analysis of the data will be performed using SAS® software, Version 9.1.3 for Windows (SAS Institute Inc., Cary, NC, USA).

### Ethics

The trial complies with the Declaration of Helsinki, and approval has been granted by the Ethics Committee of the Medical Sciences Faculty of the State University of Campinas: approval number 403/2011. The trial is registered at ClinicalTrials.gov (NCT01622465).

## Discussion

The cycle ergometer has been studied as a resource in the rehabilitation of patients with THA and TKA, but with a sample composed of both adults and older people. According to two systematic reviews on the topic, no clinical trials were found that investigated the effect of cycle ergometer-associated exercises with conventional exercises in a group composed exclusively of older patients in the postoperative period after THA [5,6].

When proposing exercise therapies for rehabilitation after THA, it should be considered that the aging process itself brings significant biological, psychological, and social decline. Decreased muscle strength and, depending on other health conditions, serious functional decline can occur [28]. Hip OA can also result in muscle imbalance, pain, and stiffness, which may further compromise function in older patients [29]. Accompanying these physical losses may be impacts on their psychological, emotional, and social aspects of quality of life [30,31].

In patients with severe hip OA, THA aims to relieve pain partially or completely and consequently allow improved function and quality of life [2]. Even considering the risks of a surgical procedure, such as infection, the benefits of THA, when properly indicated, have been demonstrated [1-3,5,6,17]. In this context, patients and professionals seek to achieve the best functional levels in the postoperative rehabilitation period. However, aspects of the rehabilitation of older patients should be considered [31]. The restoration of ROM and muscle strength may be slower because of reduced muscle elasticity and reduced ability to recruit muscle fibers [9,28].

Thus, the resources employed in physical therapy, which have been used and investigated frequently in adults, should be better understood when applied to older patients. The cycle ergometer activates the muscle groups of the hip, knee, and ankle; favors the increase and maintenance of joint ROM of the lower limbs and requires motor coordination for the execution of movements [32]. Liebs *et al*. [13] evaluated the effects of cycle ergometer-associated exercises in patients with THA and TKA in the early postoperative period. Patients performed cycle ergometer-associated exercises 3 times per week for 3 weeks. In patients with THA, pain and function, as assessed by the WOMAC, were found to be improved 3 months postoperatively in the group that performed cycle ergometer-associated exercises compared with patients who received only conventional physical therapy. No significant improvements were observed in patients with TKA.

The sessions will be supervised by the same physiotherapist and all exercises individualized, with progression guided by the patient’s function and pain level. Blood pressure and heart rate will be noted at the beginning and end of the session as well as before, during and after cycle ergometer-associated exercise.

Primary outcome measures include two instruments: the HHS for functional evaluation of the hip and the SPPB for evaluation of performance of the lower limbs. The inclusion of the HHS was justified by its frequent use in the local orthopedic community for functional hip assessments in addition to its recommendations in the literature and evidence of validity and reproducibility for patients undergoing THA [17]. These authors emphasize that this assessment system is the most widely used in the evaluation of hip arthroplasty [17]. The SPPB is an effective tool for evaluating the physical performance of the lower limbs in the older population and has been used in research on aging because of its high sensitivity in identifying changes in functionality [33,34].

The secondary outcome measures used in this trial are patient-reported outcome measures broadly applied in interventional and observational studies in patients with THA [8,10,12,13]. Recommendations that both generic and specific measures be included in the assessment of HRQOL can be found in the literature [35,36].

Some problems and limitations in conducting this trial may interfere with its effect. First, we emphasize that the participants in the intervention and the applicator will not be blinded. Second, participants in the control group, who will not perform cycle ergometer-associated exercises, will know when reading the consent form that this resource will not be used for their rehabilitation but will be used by other patients with the same condition. This may generate some disincentive; however, this feature will be offered to the control group after 10 weeks postoperatively.

Loss to follow-up may occur over the course of the study and may be considered a third limitation. The study will be conducted at a regional referral hospital where patients from neighboring cities are treated. Difficulties in transporting patients to physical therapy sessions can lead to missed sessions or the inability to continue rehabilitation at this institution. In these cases, referrals and guidance will be given for rehabilitation services in neighboring towns and patients will return to the study institution only for clinical follow-up.

Another consideration is that the exclusion criteria limit the generalization of the results to other populations. Even in the case of a pilot clinical trial, the results may not be generalized to patients with THA who are unable to perform moderate-intensity exercise, such as in cases of cardiovascular complications in the postoperative period.

This randomized clinical trial has been designed with the main purpose of evaluating the feasibility of undertaking a trial to compare the effect of cycle ergometer-associated conventional exercises to conventional exercises alone in older patients with THA. The results of the pilot trial will be used to inform the design of the future definitive study, which would provide evidence relating to the inclusion of this resource in the functional recovery of these patients. In accordance with CONSORT guidelines for reporting of clinical trials, the results will be submitted to a peer-reviewed international journal for publication irrespective of the outcome.

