### Objectives and hypotheses

The aims of this prospective, single center, randomized controlled pilot study are:to test the feasibility of undertaking a full trial clinical;to identify if the cycle ergometer will be well tolerated by older patients with THA in the early phase of rehabilitation;to test the feasibility of the proposed outcome measures;to identify effect size at end of treatment in order to calculate an appropriate sample size for the full trial clinical.

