### Intervention and follow-up periods

Assessments will be made at baseline (2 weeks postoperatively), after intervention (10 weeks postoperatively) and at 6-month follow-up (24 weeks postoperatively), and both treatment groups will have completed the intervention after 10 weeks. After the 10 weeks of supervised intervention, patients will be advised to perform some exercises unsupervised at home. In the period between the end of supervised intervention and the final evaluation (at 24 weeks), patients will be able to telephone the physiotherapist for assistance, and there will be a phone contact in the 18th week postoperatively to assess the patients' health condition.

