### Primary outcome measures

The feasibility outcome will include an evaluation of eligibility, recruitment and retention rates (in line with CONSORT recommendations), as well as monitoring of completion of outcome measures and assessments. The primary clinical outcome will be the mean change in the hip function and physical performance of the lower limbs. The instruments used will be: the HHS [15] and the SPPB [16]. The mean change in total score in these instruments between the 2 arms, as measured at baseline, 10 and 24 postoperative weeks will be the primary outcome measure.

The HHS questionnaire, an instrument that was developed to evaluate the results of THA, has been validated abroad [17] and in Brazil [18]. It consists of a scale ranging from 0 to 100 points in 4 domains: pain, function, deformity, and ROM. The maximum scores are 44 points for the pain domain and 47 for the functional domain, the latter being subdivided into activities of daily living (14 points) and gait (33 points). Domains are scored based on subjects’ responses obtained through interviews, with the exception of the deformity and ROM domains, which are evaluated by the examiner with the use of a tape measure and goniometer. The deformity domain can be scored from 0 to 4 and the ROM domain from 0 to 5, with higher scores indicating greater ROM, but within of limits for prosthesis, and less deformity. It is considered a poor functional outcome if the HHS total score is less than 70 points, fair if the score is between 70 and 79; good if the score is between 80 and 89, and excellent for 90 to 100 points [15,18].

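### Controls may start cycling after week 10, but week 24 is a primary time point, so the 24-week contrast is early versus optional later cycling

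*Protocol article*

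**What the plan says.** Under *Primary outcome measures*, the protocol article defines the primary clinical outcome as "The mean change in total score in these instruments between the 2 arms, as measured at baseline, 10 and 24 postoperative weeks", with HHS and SPPB as the instruments. *Secondary outcome measures* puts the SF-36 and WOMAC at the same time points. *Statistical analysis* plans a repeated-measures ANOVA followed by Tukey's "multiple comparison test to compare the groups at all times".

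*Randomization and allocation concealment* defines group II as receiving the conventional exercises without the ergometer. *Intervention and follow-up periods* places the later assessments "after intervention (10 weeks postoperatively) and at 6-month follow-up (24 weeks postoperatively") and describes the interval between them as follows: "After the 10 weeks of supervised intervention, patients will be advised to perform some exercises unsupervised at home". That section does not mention any ergometer offer.

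The offer appears only among the limitations in the *Discussion*. Controls will know from the consent form that other patients get the ergometer, which may discourage them, but "this feature will be offered to the control group after 10 weeks postoperatively".

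**The concern.** Week 10 is the end of supervised treatment, so on a plain reading the offer to controls opens then. Week 24 still counts toward the primary clinical outcome. From week 10 on, a control patient can receive the treatment under test while a primary assessment is outstanding. The Discussion presents the offer as a remedy for discouragement and does not name it as a threat to the 24-week result.

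Two things are at stake. First, the 24-week difference may be diluted by an amount nobody can state, since uptake is left to the patients. Second, a small or null difference at 24 weeks could be read as showing that cycling has no lasting effect, when controls had simply been allowed to catch up. The 24-week SF-36 and WOMAC comparisons share the problem, and a group-by-time test over all three visits would include the affected visit.

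**Working it through.** The article states no sample size, no power at week 24 and no expected uptake, so it has no figure to reproduce. The check has two parts.

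**1. The timing**

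| Element | Timing | Section |
|---|---|---|
| Supervised treatment ends | week 10 | Intervention and follow-up periods |
| Ergometer offered to controls | after week 10 | Discussion |
| Last assessment in the primary clinical outcome | week 24 | Primary outcome measures |
| Groups compared | at all times | Statistical analysis |
| Effect size for planning the full trial | end of treatment | Objectives and hypotheses; Statistical analysis |

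The possible exposure of controls before the last primary assessment is 24 − 10 = 14 weeks. No section delays the offer or relabels the 24-week contrast. The week-10 comparison precedes the offer and is clean. So is the planning effect size: the aim is "to identify effect size at end of treatment in order to calculate an appropriate sample size", and the sample-size calculation uses only the pre- and post-intervention times.

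**2. Illustration of the dilution**

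Assume that a share *p* of controls take up cycling after week 10 and gain a fraction *c* of its benefit by week 24. Neither value is in the article. The 24-week difference is then multiplied by (1 − *pc*).

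For scale, take a comparison that would have 80% power without any uptake. The 5% significance level is the article's; a two-sided test is assumed. The article uses 80% power for its pre/post calculation, so applying it to week 24 is also an assumption. The noncentrality is 1.960 + 0.842 = 2.802, and

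power = Φ(2.802 × (1 − *pc*) − 1.960).

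| *p* | *c* | Share of difference left | Power |
|---|---|---|---|
| 0 | – | 100% | 80% |
| 0.10 | 0.5 | 95% | 76% |
| 0.10 | 1 | 90% | 71% |
| 0.25 | 0.5 | 87.5% | 69% |
| 0.25 | 1 | 75% | 56% |
| 0.50 | 0.5 | 75% | 56% |
| 0.50 | 1 | 50% | 29% |

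For example, *p* = 0.25 and *c* = 0.5 gives 2.802 × 0.875 − 1.960 = 0.492, and Φ(0.492) = 0.69.

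On the article's own scale, a medium effect is 0.75 SD, for which 28 patients per arm give 80% power (normal approximation, 1:1). At *p* = 0.50 and *c* = 0.5 the effect falls to 0.75 × 0.75 = 0.56 SD, and the same 28 per arm give 56%.

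**The case against.** The strongest reply is that contamination is possible but not shown. The only basis is one clause in the Discussion, and it sets an earliest time without a dose or schedule. *Interventions* allows ergometer exercise only with a professional present, while the plan for weeks 10 to 24 is unsupervised home exercise with telephone support. The article also notes that transport to sessions is difficult for patients from other towns. Uptake before week 24 could therefore be low, and at 10% uptake the loss is small.

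Further, this is a pilot. Feasibility is its main purpose, none of its four stated aims is a 24-week efficacy test, and the planning effect size comes from the end of treatment. The power figures describe no planned property of the trial. A 24-week difference in favour of cycling would still be informative: if late cycling only helps controls, that difference is conservative. Details of the offer may also sit in the full protocol.

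Most of this stands as a limit on size. It does not remove the conflict. The article itself fixes both the primary time points and the offer, and on its wording they overlap. Randomisation still gives a valid comparison at 24 weeks, but of access policies (early or optional later cycling), whatever the uptake turns out to be. Pilot status does not make a null week-24 result easier to read. The article tests at 5%, commits to submitting the results whatever they show, and will use them to design the definitive trial, where the same arrangement could be repeated.

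**Conclusion.** The concern holds, and it is confined to week 24. As written, the primary clinical outcome includes a time point at which controls may already have received the ergometer, so that contrast does not estimate cycling against no cycling. The expected direction is toward zero, assuming later cycling helps controls. The size is unknown: from a small loss at 10% uptake (power 71% to 76% for a comparison that would have had 80%) to a serious one at 50% uptake (29% to 56%), with catch-up from half to full. These figures rest on assumed uptake and catch-up and serve only to show the scale. A null result at 24 weeks would be hard to interpret; a result favouring cycling would probably be an underestimate. The feasibility aims, the 10-week comparison and the planning effect size stand. It should be fixed, because the remedy is simple and a primary time point is affected.

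**What to change.** Choose one of two changes.

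**Option 1.** Make the 10-week between-arm change in HHS and SPPB the primary clinical comparison, in line with the end-of-treatment effect size named in the aims. Report week 24 as a secondary contrast labelled *early versus optional later cycling*, and do the same for the 24-week SF-36 and WOMAC. Record ergometer use from week 10 to week 24 in both arms. The existing schedule helps here, since "there will be a phone contact in the 18th week postoperatively"; a question on use could be added to that call and to the 24-week visit. The cost is a documented change to the primary outcome of a registered trial that began in August 2011, and giving up a 24-week claim about cycling versus no cycling.

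**Option 2.** Keep the outcome as it is and state that the ergometer is offered to controls only after their 24-week assessment. The cost is a wait 14 weeks longer for controls, which may add to the discouragement the Discussion describes. This option also helps only controls who have not yet had the offer, so ergometer use should still be recorded for the others.

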## Trial status

The trial began in August 2011. Participant recruitment will likely be completed after 2 years.

## Abbreviations

ANOVA: analysis of covariance
CONSORT: Consolidated Standards of Reporting Trials
HHS: Harris Hip Score
HRQOL: health-related quality of life
OA: osteoarthritis
ROM: range of motion
SAS: Statistical Analysis System
SF-36: Medical Outcomes Study 36-Item Short-Form Health Survey
SPPB: Short Physical Performance Battery
THA: total hip arthroplasty
TKA: total knee arthroplasty
WOMAC: Western Ontario and McMaster Universities Osteoarthritis Index.
